### Objectives {7}

The primary objective is the number of patients in sinus rhythm 48 h after the first episode of POAF after cardiac surgery. The secondary objectives are the hemodynamic tolerance, the ICU and hospital length of stay, and the recurrence of POAF and/or thromboembolic complications and/or hemorrhagic complications and/or number of patients with an adverse event due to landiolol or amiodarone, within 2 months and 1 year after surgery. Table 1 summarizes the objectives and time points.

**Table 1 Tab1:** Objectives

	Outcomes	Measurements	Time points
Primary	Proportion of patient in sinus rhythm at 48 h	Number (percentage) of patients	48 h
Secondary	Hemodynamic tolerance of treatment	Incidence of MAP < 60 mmHg and/or bradycardia as heart rate < 40/min	ICU LOS
	ICU LOS	Total days	ICU LOS
	Hospital LOS	Total days	Hospital LOS
	Recurrence of PoAF	EKG	2 months and 1 year
	Thromboembolic complications	Stroke or embolic ischemia	2 months and 1 year
	Hemorrhagic complications	Active bleeding uncontrollable, with hemodynamic instability, with an urgency treatment, or in a location with functional or vital prognosis	2 months and 1 year
	Adverse events to amiodarone or beta-blockers		2 months and 1 year

*EKG* Electrocardiogram, *ICU* Intensive care unit, *LOS* Length of stay, *MAP* Mean arterial pressure

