**Fig. 1 Fig1:**
[figure not shown]
Flowchart of the FAAC study

In the landiolol group (Fig. 2), landiolol is administered intravenously without bolus at a starting dose of 2.5 μg/kg/min. This dose is increased by steps of 2.5 μg/kg/min every 10 min until a maximum dose of 80 μg/kg/min in order to reach a target heart rate (HR) of less than 90 beats per minute (bpm) [6]. Once this target heart rate is achieved, beta-blocker therapy is bridged within 24 h of landiolol infusion with bisoprolol 1.25 mg twice daily if the maximum dose of landiolol was inferior to 15 μg/kg/min or bisoprolol 2.5 mg twice daily if the maximum dose of landiolol was superior to 15 μg/kg/min (Additional file 3). Landiolol infusion is then discontinued.

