**Fig. 2 Fig2:**
[figure not shown]
Landiolol group algorithm. IV, intravenous; PoAF, postoperative atrial fibrillation

In the amiodarone group (Fig. 3), amiodarone is administered intravenously with a bolus of 5–7 mg/kg over 1 h and a subsequent continuous infusion of 1.0 g per day until reduction to sinus rhythm [3]. If reduction to sinus rhythm occurs or if the target heart rate drops below 90 beats per minute, intravenous infusion of amiodarone is discontinued and bridged via oral route with 200 mg amiodarone daily.

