**Fig. 3 Fig3:**
[figure not shown]
Amiodarone group algorithm. IV, intravenous; PoAF, postoperative atrial fibrillation

For both groups, the curative anticoagulation is started if PoAF is > 48 h and the CHA_2_DS_2_-VASc score is ≥ 1 (for men) or ≥ 2 (for women) [10]; the treatment (bisoprolol or amiodarone) is continued for 2 months, until cardiology consultation for evaluating the treatment and the anti-coagulation prescription [11].

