#### Secondary outcomes

The secondary outcomes are hemodynamic stability (hypotension, bradycardia), duration of stay in the ICU and in the hospital, number of patients (in percentage, 95% CI) with a recurrence of PoAF within 2 months and 1 year after surgery, number of patients (in percentage, 95% CI) with a thromboembolic complication within 2 months and 1 year after surgery, number of patients (in percentage, 95% CI) with a hemorrhagic complication within 2 months and 1 year after surgery, and number of patients (in percentage, 95% CI) with an adverse event due to landiolol or amiodarone within 2 months and 1 year after surgery.

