## Data collection and management

### Plans for assessment and collection of outcomes {18a}

Data, patients’ consent, and outcomes will be recorded by the care provider in charge of the patient and a dedicated local research coordinator before and after enrollment using eCRFs (Ennov Clinical®).

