### Adverse event reporting and harms {22}

In France, the competent authority qualified this research as “research with minimal constraint.” This means that adverse events are not reported to the sponsor, only new safety information, i.e., if the investigator considers that the risk–benefit balance of the study should be reviewed.

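### The adverse-event outcome has two incompatible definitions, and the one in the text, read literally, leaves out events from the landiolol arm's two months of bisoprolol

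*Protocol article*

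**What the plan says.** The text of Objectives {7} sets as one secondary objective the "number of patients with an adverse event due to landiolol or amiodarone, within 2 months and 1 year after surgery". Secondary outcomes, under Outcomes {12}, repeats this: patients "with an adverse event due to landiolol or amiodarone within 2 months and 1 year after surgery". Table 1, which sits in {7} and summarises the objectives, names the same outcome as "Adverse events to amiodarone or beta-blockers", with the same two time points.

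Intervention description {11a} sets the drugs to which each arm is exposed. In the landiolol arm, "beta-blocker therapy is bridged within 24 h of landiolol infusion with bisoprolol", and the infusion then stops. In the amiodarone arm, "intravenous infusion of amiodarone is discontinued and bridged via oral route with 200 mg amiodarone daily". For both arms, "the treatment (bisoprolol or amiodarone) is continued for 2 months".

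On collection, {18a} states that "outcomes will be recorded by the care provider in charge of the patient and a dedicated local research coordinator", using the electronic case report form (eCRF). Section {17a} says that care providers know the allocation. Section {22} says of the study's French regulatory category: "This means that adverse events are not reported to the sponsor, only new safety information".

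**The concern.** An adverse-event outcome that depends on drug attribution compares the arms fairly only if the list of drugs covers each arm's whole treatment course. The Table 1 list does, because bisoprolol is a beta-blocker. The list in the text names amiodarone, which is both the intravenous and the oral drug of its arm, but for the other arm it names only the infusion drug. Section {6a} gives landiolol a half-life of 4 minutes, so little that happens between the first days and 2 months could be attributed to it.

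Two analysts working from the same article could therefore report different safety results. The one who followed the text literally would produce a comparison tilted towards the experimental arm. Attribution is also a causal judgement made by people who know the allocation, so wording that leaves room for choice is a weak point.

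**Working it through.** **Step 1: set the definitions against the exposure.**

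| Phase | Drug | Counted by the text of {7} and {12}? | Counted by Table 1? |
|---|---|---|---|
| Landiolol arm, infusion | landiolol | yes | yes |
| Landiolol arm, oral, 2 months | bisoprolol | no, if read literally | yes |
| Amiodarone arm, infusion | amiodarone | yes | yes |
| Amiodarone arm, oral, 2 months | amiodarone | yes | yes |

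The definitions differ in one cell only, and that cell is the landiolol arm's oral phase.

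**Step 2: inputs for size.** The article states no adverse-event rate and no power for this outcome, so there is no plan figure to reproduce. The documented inputs are 175 patients per arm (Sample size {14}) and the two-sided 5% level ({20a}). Two inputs are assumed:

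- *p*, the true risk of a drug-related event, equal in both arms: 5%, 10% or 20%.
- *s*, the share of landiolol-arm events due to bisoprolol: 25%, 50% or 75%.

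**Step 3: formulas.** The amiodarone arm is counted at *p* and the landiolol arm at *q* = *p*(1 − *s*), so the false difference is *d* = *p* − *q* = *ps*. With *m* = (*p* + *q*)/2 and *n* = 175:

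- SE₀ = √[2*m*(1 − *m*)/*n*]
- SE₁ = √[(*p*(1 − *p*) + *q*(1 − *q*))/*n*]
- Chance of a significant result favouring landiolol = Φ[(*d* − 1.96 SE₀)/SE₁]

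Worked case, *p* = 10% and *s* = 50%: *q* = 5%, *d* = 5 points, *m* = 7.5%, SE₀ = 0.02816, SE₁ = 0.02803. Then (0.05 − 1.96 × 0.02816)/0.02803 = −0.185, and Φ(−0.185) = 0.43.

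**Step 4: results under the literal text wording.** Each cell gives the false difference in percentage points, then the chance of significance.

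| True risk *p* | *s* = 25% | *s* = 50% | *s* = 75% |
|---|---|---|---|
| 5% | 1.25; 8% | 2.5; 23% | 3.75; 52% |
| 10% | 2.5; 13% | 5; 43% | 7.5; 83% |
| 20% | 5; 23% | 10; 75% | 15; 99% |

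Under the Table 1 wording bisoprolol events are counted, so *q* = *p* and the false difference is zero in every cell. The formula is a normal approximation to the chi-square test. In the low-risk cells, where expected counts are small, the Fisher exact test that {20a} also allows would reject somewhat less often.

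**The case against.** The best reply is that the text can be read as shorthand for the two strategies. The arms are called the landiolol and amiodarone groups, {6b} says that the trial compares amiodarone with beta-blockers, and time points of 2 months and 1 year make little sense for a drug cleared in minutes. Table 1 is current text too, and it is symmetric. This stands in part. The document is ambiguous, so it would be wrong to say that the safety comparison is one-sided as the plan is written: only one of the two wordings is, and only when read literally. But a strategy reading is a guess about intent, and the literal wording appears twice, including in the section that defines the outcomes.

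A reader might also infer three stronger points that the documents do not support:

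- *That {22} makes the comparison one-sided, or rules the outcome out.* It applies equally to both arms and describes safety reporting under a regulatory category. Collection of outcomes is a separate matter: {18a} and {19} have them recorded at the sites in the eCRF and managed by the sponsor. The wording sits awkwardly beside an adverse-event outcome, but no more than that.
- *That this is the only comparative safety evidence.* Haemodynamic tolerance, thromboembolic complications and haemorrhagic complications are separate secondary outcomes, which Table 1 defines without attribution to a drug.
- *That a false positive is nearly certain.* Assuming 10% of events in the amiodarone arm against 1–2% counted in the landiolol arm gives a chance of 96–89%. That is one scenario, in which 80–90% of landiolol-arm events go uncounted. The grid above shows how far the answer depends on such assumptions.

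Finally, an article may leave the details of event definition and attribution to the full protocol. That would excuse silence, but here the article states the outcome twice and the statements disagree.

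**Conclusion.** The inconsistency is real and should be corrected. The text of {7} and {12} and the entry in Table 1 define different outcomes, and because of the switch to bisoprolol in {11a} the difference falls on one arm only. Applied literally, the text would bias this secondary safety comparison towards landiolol; Table 1 would not.

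The direction follows from the documents, but the size does not. With equal true risk of 5–20% and a bisoprolol share of 25–75%, both assumed, the false difference at 175 per arm is 1.25–15 points, and it is significant in about 8–99% of trials. The point is confined to one secondary outcome.

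**What to change.** Use one definition in the text of {7}, in {12} and in Table 1: patients with an adverse event attributed to any drug of the study strategies (landiolol, bisoprolol or amiodarone), counted identically in both arms over the same period, at 2 months and at 1 year.

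Two additions are optional:

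- Report an all-cause count as a supplement, because attribution is made by unblinded care providers.
- Add a sentence to {22} that separates safety reporting to the sponsor from eCRF capture of this outcome.

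The cost is a change of wording and a check that the eCRF page records bisoprolol events. Treatment and sample size do not change. It is best done while recruitment is open, because events that sites did not record may not be recoverable later.

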### Participant timeline {13}

Additional file 4 summarizes the schematic diagram of study procedures.

### Sample size {14}

Two groups of 159 patients (318 patients in total) are needed to show an increase from 70 to 85% of patients in sinus rhythm 48 h after the first episode of PoAF [4, 8], using a two-sided α-risk at 5% and a power at 90%. Considering the uncertainty in the effect size, we need to include a total of 350 patients (175 patients per arm).

### Recruitment {15}

Recruitment will be conducted in collaboration with eleven public and private hospital in France, experienced with both amiodarone and landiolol use in clinical routine. The principal investigator and scientific responsible will introduce the study to healthcare staff (anesthesiologists, intensivists, cardiac surgeons, cardiologists, and nurses) with clinical research support, as part of their clinical team meetings in all recruiting organizations, and will tailor brochures targeted specifically for healthcare providers and patients. A newsletter will be realized and sent to all participants and healthcare providers in each participating hospital.

## Assignment of interventions: allocation

### Sequence generation {16a}

The biostatistician of the sponsor CHU de Caen will perform the randomization list. The randomization sequence is generated using permutated blocks of varying size and stratified by center, using R software version 4.0.5 (2021 The R Foundation for Statistical Computing). The randomization was centralized in a computer using the e-clinical platform.

### Concealment mechanism {16b}

There is no blinding in this open-label study (care providers know the group allocation, but the patient and the surgeon are not aware of the group allocation).

### Implementation {16c}

Randomization is performed by the anesthesiologist in charge of the patient in the cardiac ICU using CSOnline website (Ennov, Paris, France), 24/7 available.

## Assignment of interventions: blinding

### Who will be blinded {17a}

Patients are blinded of the study group. Care providers are aware of the group allocation.

### Procedure for unblinding if needed {17b}

As only patients were blinded of the allocation group, this is a simple blinded study.

## Data collection and management

### Plans for assessment and collection of outcomes {18a}

Data, patients’ consent, and outcomes will be recorded by the care provider in charge of the patient and a dedicated local research coordinator before and after enrollment using eCRFs (Ennov Clinical®).

### Plans to promote participant retention and complete follow-up {18b}

Data from patients who will be pulled out of the study because of refusal to participate, refusal of the follow-up evaluation, or because of any other reasons as decided by the main investigators will be analyzed according to their initial assigned group on an intention-to-treat analysis.

### Data management {19}

The data manager of the University Hospital of Caen is responsible for the development, sponsor database development, and data management.

Data will be collected and registered using electronic CRFs (Ennov Clinical®) in each center by dedicated local technical research. A research coordinator will centralize data from all sites.

### Confidentiality {27}

Study data will be collected only by authorized staff (study investigator, local research coordinator, or any person who has authorization as scheduled by the study protocol). Data will be stored in a local database accessible only to those who have authorization as scheduled by the study protocol. Access to the database will be with a personal login and password. Login to the database will be saved in the database’s login history folder.

The University Hospital of Caen conforms to the National Informatic and Liberty French Laws, and, therefore, patient confidentiality will be protected.

### Plans for collection, laboratory evaluation, and storage of biological specimens for genetic or molecular analysis in this trial/future use {33}

Not applicable.

## Statistical methods

### Statistical methods for primary and secondary outcomes {20a}

Categorical variables will be described as count, percentages, and 95% confidence interval, and continuous variables will be described as mean (standard deviation) or median [interquartile range], as appropriate. The analysis for the primary outcome will follow the intention-to-treat principle in which all the randomized patients will be analyzed in the assigned group, using the chi-square test or the Fisher exact test. Secondary outcomes will be analyzed with a chi-square test or a Fisher exact test for categorical variables and with a Student’s *t*-test or a Mann–Whitney *U* test for continuous variables according to their distributions. No sub-group analysis is planned. A two-tailed *p* < 0.05 is considered statistically significant. All statistical analysis will be conducted with SAS V9.4 (SAS Institute, Cary, NC).

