## Methods: participants, interventions, and outcomes

### Study setting {9}

Patients are recruited in eleven French institutions (details in Additional file 2). The study sponsor is the Research and Innovation Department of the University Hospital of Caen, a public academic institution in France.

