### Intervention description {11a}

Patients who underwent cardiac surgery and have a de novo persistent POAF (for at least 30 min) in the cardiac intensive care unit (ICU) and are eligible for the study are randomized after informed consent, after exclusion of hypovolemia and pericardial effusion with a transthoracic echocardiography and after exclusion of dyskalemia or anemia with an arterial blood gas performed in routine care. Randomization is performed by the anesthesiologist in charge of the patient in the cardiac ICU using CSOnline website (Ennov, Paris, France), 24/7 available. The randomization sequence is generated by the statistician of the study using permutated blocks and stratified by center. Patients are randomized in either the landiolol group or the amiodarone group (Fig. 1).

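### Randomisation is stratified by center but the primary test ignores center: conservative if centers differ, and a free, minor improvement to correct

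*Protocol article*

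**What the plan says.** Two sections of the protocol article describe the allocation in the same way. Sequence generation {16a} states: "The randomization sequence is generated using permutated blocks of varying size and stratified by center". Intervention description {11a} repeats that the list is made "using permutated blocks and stratified by center". Study setting {9} gives the number of strata: "Patients are recruited in eleven French institutions".

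Statistical methods {20a} then fixes the primary analysis by intention to treat: "all the randomized patients will be analyzed in the assigned group, using the chi-square test or the Fisher exact test". For the other outcomes it says "Secondary outcomes will be analyzed with a chi-square test or a Fisher exact test for categorical variables", with a t-test or Mann-Whitney test for continuous variables. The threshold is also set: "A two-tailed *p* < 0.05 is considered statistically significant". None of these tests includes center. Sections {20b} and {20c} announce sensitivity analyses and name multiple imputation for missing data. They name no center-adjusted analysis.

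The tests are therefore stated, not left open, and they leave out the only stratification factor that the protocol names.

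**The concern.** Permuted blocks within center force the arms to be nearly equal in size in every center. Differences between centers then largely cancel out of the treatment contrast. The crude chi-square test does not use this: its variance comes from the pooled proportion and still contains the between-center variation. If centers differ in conversion rate, the standard error is larger than the randomisation warrants. The test then rejects a true null hypothesis less often than 5%, and some power is given up.

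At stake is a small loss of efficiency and an analysis that does not match the design. The validity of a positive result is not at stake.

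**Working it through.** **Inputs from the protocol article.** 70 versus 85% in sinus rhythm at 48 h, two-sided α 5%, power 90%, 159 per arm (318 in total) raised to 175 per arm (350) (Sample size {14}); eleven centers ({9}); permuted blocks stratified by center ({11a}, {16a}).

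**Inputs assumed, because the documents give no figure.** Between-center SD on the logit scale from 0 to 1.0; unequal center sizes, from 25% down to 2% of patients; blocks of 4.

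**1. The plan's own sample size.** With a pooled variance under the null:

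n = [1.960·√(2·0.775·0.225) + 1.2816·√(0.70·0.30 + 0.85·0.15)]² / 0.15² = (1.1575 + 0.7445)² / 0.0225 = 160.8, so 161 per arm.

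The arcsine formula gives 158.7, so 159 per arm, which is the stated figure. By the usual normal approximation, power is 89.7% at 159 per arm and 92.3% at 175. The stated size reproduces as an unstratified two-proportion comparison.

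**2. Why the crude test is conservative.** Let p_k be the rate in center k under the null and p̄ the mean. Then

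p̄(1 − p̄) = mean of p_k(1 − p_k) + Var(p_k).

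The crude test uses the left side. With near-equal arms within each center, the true variance of the contrast needs only the first term on the right. The ratio of true to assumed variance is therefore about 1 − Var(p_k)/[p̄(1 − p̄)].

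A hand check at logit SD 0.5, first-order approximation: Var(p_k) ≈ (0.5 × 0.70 × 0.30)² = 0.0110, and 0.0110/0.21 = 0.0525. The effective critical value is 1.960/√(1 − 0.0525) = 2.014, a two-sided type I error of about 4.4%. This is close to the simulated value below.

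**3. Simulation.** 40,000 trials per cell, N = 350, normal center effect on the logit, marginal rates held at 70% versus 70% (null) or 70% versus 85% (alternative). The crude chi-square is compared with the CMH test stratified by center.

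| Assumed logit SD | Central 80% of centers, at a mean of 70% | Type I error, crude | Type I error, CMH | Power, crude | Power, CMH |
|---|---|---|---|---|---|
| 0 | 70–70% | 5.1% | 5.1% | 92.8% | 92.7% |
| 0.3 | 62–78% | 4.8% | 5.0% | 92.6% | 92.7% |
| 0.5 | 56–82% | 4.6% | 5.1% | 92.8% | 93.1% |
| 0.8 | 48–88% | 4.1% | 5.1% | 93.1% | 94.1% |
| 1.0 | 43–91% | 3.5% | 4.8% | 92.9% | 94.5% |

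The simulation standard error is about √(0.05·0.95/40,000) = 0.11 points for type I error and √(0.93·0.07/40,000) = 0.13 points for power. The power gain from stratifying is thus nil at SD 0 and 0.3 within simulation error, about 0.3 points at 0.5, about 1.0 at 0.8 and about 1.5 at 1.0.

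At N = 318 the crude type I error runs from 5.0% to 3.6% over the same range, and the power gain from 0 to 2.0 points.

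**The case against.** The strongest reply is that nothing is lost that the plan promised. The sample size was derived for the unstratified comparison, and that comparison keeps about 93% power at N = 350 in every scenario. Any departure from nominal error is conservative, so a significant result stands. The effect exists only if centers differ, and the documents say nothing about how much. An SD of 1.0 is extreme for a narrowly selected population treated by algorithm. All of this stands, and it is why the point is minor.

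It does not remove the point. The stated test does not match the stated randomisation. In the simulations the stratified test held its error at about 5% and lost nothing material when centers were alike.

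Four stronger readings might be inferred and are not supported:

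- **That the error rate is certainly off nominal.** With no center effect the two tests agree.
- **That power falls materially.** Larger gains appear only if a treatment effect smaller than 70 versus 85% is assumed, and the protocol plans for no such effect.
- **That the secondary analyses are shown to suffer in the same way.** Fisher's test, the t-test and the Mann-Whitney test were not simulated.
- **That the trial will report a p-value with no interval for the treatment difference.** The article commits to 95% confidence intervals for percentages. The effect measure and its interval are normally set out in the statistical analysis plan, which is not shown, so silence here is not an error.

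**Conclusion.** The mismatch is on the page: allocation is stratified by center and the primary test is not. Its consequence is conditional and small. If centers differ, the crude test is conservative, with type I error of about 4.6% at an assumed logit SD of 0.5 and 3.5% at 1.0. Stratifying would add about 0.3 and 1.5 points of power respectively at the planned effect and N = 350.

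These sizes rest on assumed between-center variation, center sizes and block length. The direction and the absence of false-positive inflation follow from the design and not from those values. This is a free improvement of minor severity, and no change in sample size is called for.

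**What to change.** In {20a}, make the primary analysis a CMH test stratified by randomisation center, reported with the Mantel-Haenszel risk difference and its 95% CI. State a rule for pooling very small centers and fix it before database lock, because a center with patients in one arm only contributes nothing to the stratified test. Keep the crude chi-square test as a sensitivity analysis. Secondary outcomes can use the same stratification for consistency, although the gain there has not been quantified.

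The cost is text only: center is known for every patient from the randomisation, and no patients or data are added. If the change is made in the protocol, it follows the ethics and regulatory route for modifications described in {25}. The article gives recruitment as ongoing and database closure at the end of 2024, so on its own timeline the change can precede the analysis.

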### Eligibility criteria {10}

Patients scheduled for cardiac surgery are eligible for the study.

Inclusion criteria are:Adult patients hospitalized in the cardiac intensive care unit after cardiac surgery including coronary artery bypass and/or aortic valve repair and/or ascending aorta surgery;New onset of postoperative atrial fibrillation persistent more than 30 min;Patient with a social security number;Patient with written informed consent.

Exclusion criteria are:Patients with hemodynamic instability with the need of an electrical cardioversion;Preoperative treatment with anticoagulant therapy;Contra-indication to amiodarone or beta-blockers;Sepsis;Slow PoAF (heart rate < 90/min);Patient with inotropic support;Patient history of atrial fibrillation;Emergency surgery, ventricular assist device, heart transplantation, TAVR, mechanical valve, mitral valve, or tricuspid valve repair.

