### Outcomes {12}

#### Primary outcome

The primary outcome is the number of patients (in percentage, 95% CI) in sinus rhythm 48 h after the first episode of PoAF after cardiac surgery. This primary outcome was chosen to compare the efficacy of both landiolol and amiodarone to reduce PoAF in the first 48 h which is the delay recommended to start the anticoagulation if PoAF is not reduced [3].

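### The primary test is valid and adequately powered, but it uses no baseline values the trial already needs; prespecified adjustment would cost little and might gain some power

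*Protocol article*

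**What the plan says.** Statistical methods {20a} fixes the primary analysis: all randomised patients in their assigned arm, "using the chi-square test or the Fisher exact test". No covariate is named. Methods for additional analyses {20b} rules out subgroup analyses and plans several sensitivity analyses, with multiple imputation the only one named.

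Sample size {14} is built on the same crude comparison: "Two groups of 159 patients (318 patients in total) are needed". The target there is a rise in the sinus-rhythm rate from 70% to 85%. It raises the total to 350 because the effect size is uncertain.

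Other sections depend on facts about the patient before treatment:

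- **Heart rate.** Eligibility criteria {10} excludes "Slow PoAF (heart rate < 90/min", so the rate must be checked at entry.
- **Type of surgery.** The same section defines the population by operation.
- **Time of AF onset.** AF must have lasted more than 30 minutes, and the primary outcome is the proportion "in sinus rhythm 48 h after the first episode of PoAF". Both need an onset time.
- **Age and sex.** The anticoagulation rule for both groups uses a score with sex-specific cut-offs: "the CHA_2_DS_2_-VASc score is ≥ 1 (for men) or ≥ 2 (for women". It applies only when AF exceeds 48 h.

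Plans for assessment and collection of outcomes {18a} says data are recorded before and after enrolment, but the article does not list the fields.

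**The concern.** Whether AF ends within 48 h could well depend on age, operation, ventricular rate and how long AF has already lasted. Time from onset to randomisation also sets how much of the 48 h remains for the allocated drug. If such values predict the outcome, a two-by-two test leaves their share of the variation in the noise. A model fixed in advance would remove it with almost no new data.

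The stake is power if the true effect is below 15 points, a possibility that the Sample size section admits. This is a stated choice of method, not a detail left out of the article: an SAP that follows the published sentence would run the crude test.

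**Working it through.** **1. Reproduce the plan's figure.** Inputs from Sample size {14}: p1 = 0.70, p2 = 0.85, two-sided α = 5%, power 90%. Mean proportion 0.775.

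n per arm = [1.960·√(2·0.775·0.225) + 1.282·√(0.70·0.30 + 0.85·0.15)]² / 0.15² = [1.960·0.5906 + 1.282·0.5810]² / 0.0225 = 161.

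The unpooled formula gives 158 and the arcsine formula 158.7, which rounds up to the stated 159. The plan's figure is reproduced, and it belongs to a crude comparison.

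**2. Power of the crude test at 175 per arm.** Power = Φ[(0.15·√175 − 1.960·0.5906) / 0.5810] = Φ(1.42) = 92.3%. Exact enumeration gives 92.6% for chi-square and 90.6% for Fisher. About 350 × 0.225 / 2 = 39 non-events per arm are expected, so Fisher is not needed for small cells.

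For 70% against 80% (an assumed smaller effect), Φ[(0.10·√175 − 1.960·√0.375) / √0.37] = Φ(0.20) = 58%.

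**3. Approximate gain from adjustment.** Let R² be the share of outcome variance explained by baseline values. The documents give no figure, so 2% to 20% is assumed. Adjusted power is approximated by using 175/(1 − R²) per arm in the formula of step 2.

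| Assumed R² | Power at +15 points | n per arm for 90% power |
|---|---|---|
| 0 (crude) | 92.3% | 161 |
| 2% | 92.8% | 158 |
| 5% | 93.5% | 153 |
| 10% | 94.6% | 145 |
| 20% | 96.6% | 129 |

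An R² of 1 − 318/350 = 9% would be worth the 32 patients added for uncertainty.

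**4. Simulation, including the weak end.** 175 per arm, control rate 70%, crude test against the test of treatment in a logistic model. The prognostic score has an assumed SD on the logit scale. Rows marked * come from 3,000 trials per setting with six estimated covariates. The others come from 4,000 trials with one score plus three pure-noise covariates.

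| Logit SD (c-statistic) | +15 points: crude / adjusted | +10 points: crude / adjusted |
|---|---|---|
| 0 | 92.3 / 91.9% | 57.9 / 57.6% |
| 0.2* (0.56) | 93.1 / 93.0% | 59.7 / 59.4% |
| 0.35* (0.60) | 91.6 / 92.4% | 56.9 / 57.6% |
| 0.5 (0.63) | 92.6 / 93.4% | 57.3 / 58.9% |
| 0.8 (0.70) | 92.2 / 94.3% | 59.3 / 64.4% |
| 1.2 (0.78) | 92.1 / 95.8% | 57.2 / 66.0% |

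Crude power should not depend on the SD, so its spread down each column is simulation noise. The largest gains are 95.8 − 92.1 = 3.7 points and 66.0 − 57.2 = 8.8 points. With useless covariates the loss is 0.3 to 0.4 points. In the 4,000-trial runs type I error was 5 to 6% for both methods, within or near simulation error.

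A repeat of the noise-covariate design at +15 points gave 92.0 / 91.7% (SD 0), 92.4 / 92.4% (0.35), 93.0 / 93.6% (0.5), 92.4 / 94.4% (0.8) and 93.1 / 96.6% (1.2), the same picture.

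**The case against.** The strongest reply is that nothing here is wrong. The crude test holds its type I error, matches the sample-size calculation and exceeds the 90% target. That stands, so a reader should not infer that the test is invalid or the trial underpowered for its stated effect.

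Four other inferences also go too far:

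- **That these values are shown to be prognostic.** No section says so. The Discussion stresses hyperadrenergic drive and excludes mitral and tricuspid repair because AF arises differently there. That makes heart rate and operation plausible predictors, no more. Narrow eligibility may also limit their spread.
- **That all are recorded at baseline.** The article lists no eCRF fields, and the anticoagulation score is needed only when AF exceeds 48 h. Heart rate, operation and onset time must be known; a stored field for each is an inference.
- **That the open design makes baseline imbalance worse.** Randomisation is central, and the crude test already allows for chance imbalance.
- **That the change is free.** The test is published, recruitment began in January 2020, and care providers who know the allocation also record outcomes. A change needs a date and a reason.

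The SAP is not shown, and the sensitivity analyses are an open list, so an adjusted supportive analysis may already exist. It would still not alter the primary test. What survives the objection is an unequal trade: a small possible loss against a larger possible gain.

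**Conclusion.** The point holds as a recommendation on efficiency. At the planned effect the gain lies between nil and about 4 points, from a base of about 92%. At a 10-point effect it lies between nil and about 9 points, from a base of about 58%. The upper ends need a logit SD of 1.2, which nothing in the documents supports or excludes. At an SD of 0.35 or less, the gain is under a point at either effect. If the covariates carry no information, the cost is about a point or less.

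These figures assume a correctly specified logistic model, one combined score and complete data. Use of centre, the stratification factor, is a separate question and is not counted here.

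**What to change.** By a dated amendment, or in an SAP fixed before any comparative data are seen, make the primary analysis a logistic regression of sinus rhythm at 48 h on treatment. Name a short covariate list: age, type of surgery, heart rate at randomisation, and time from AF onset to randomisation. Limit it to items confirmed to be in the eCRF.

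Report the standardised risk difference with its 95% CI, which keeps the result on the scale of the sample-size calculation. State whether the primary p-value comes from that difference or from the treatment coefficient, so that test and interval do not disagree. Keep the crude comparison as supportive and name it as chi-square, which settles the open choice with Fisher.

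The cost is the amendment or SAP text and a few lines of SAS. The downsides are a headline result that depends on a model and a simple imputation rule for rare missing covariates.
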